| Physical examination                            | X                                    |                                     | Including weight and vital signs (example: temperature, blood pressure, pulse rate, respiration rate)                                                                                                                                                                                                                                                                                                                                                                                     |
| Prior and current medication                    | X                                    |                                     |                                                                                                                                                                                                                                                                                                                                                                                                                                                                                           |
| AE collection                                   | X                                    | X                                   | CTCAE Version 4.0. During long-term follow-up, only SAEs that are related to study regimen or protocol procedure will be collected. All drug- or procedure-related AEs and SAEs should be followed until they resolve, are no longer considered to be drug- or procedure-related, become stable or return to baseline, the patient starts a new therapy, the patient dies, or the patient becomes lost to follow-up. Frequency of evaluation is left to the judgment of the investigator. |
| ECOG performance status                         | X                                    |                                     |                                                                                                                                                                                                                                                                                                                                                                                                                                                                                           |

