| MDASI* questionnaire                                              | X                                                         |                                     | Patients should complete before interaction with site staff                                                                                                                                                                                                |
| Sample collection                                                 | For all sample collection, see Appendix 4 |                                     |                                                                                                                                                                                                                                                            |
| Biomarkers                                                        |                                                           |                                     |                                                                                                                                                                                                                                                            |

Abbreviations: AE = adverse event; aPTT = activated partial thromboplastin time; CT = computer tomography; CTCAE = Common Terminology Criteria for Adverse Events (NCI 2009); ECOG = Eastern Cooperative Oncology Group; INR = international normalized ratio; irRECIST = immune-related Response Evaluation Criteria in Solid Tumors; MDASI = MD Anderson Symptom Inventory questionnaire, \*= inclusion of a supplemental sheet consisting of 2 additional items (worst cough and worst diarrhea); MRI = magnetic resonance imaging; PT = prothrombin time; RECIST 1.1 = Response Criteria in Solid Tumors Version 1.1; SAE = serious adverse event.

a Short-term follow up starts the day after the patient and the investigator agree that the patient will no longer continue study treatment and ends when final safety assessments are completed 30 days ( $\pm 7$ ) after last dose of study drug.

b Long-term follow up begins the day after short-term follow up is completed and continues every 90 days until the patient's death or overall study completion.

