**Figure JPCE.7.1. Continued access diagram.**

Patients who are in short-term follow-up when the continued access period begins will continue in short-term follow-up until the 30-day short-term follow-up visit is completed. Long-term follow-up does not apply.

Patients who are in long-term follow-up when the continued access period begins will be discontinued from long-term follow-up.

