### **9.2.1. Serious Adverse Events**

An SAE is any AE from this study that results in one of the following outcomes:

- death
- initial or prolonged inpatient hospitalization
- a life-threatening experience (that is, immediate risk of dying)
- persistent or significant disability/incapacity
- congenital anomaly/birth defect
- considered significant by the investigator for any other reason: important medical events that may not result in death, be life-threatening, or require hospitalization may be considered serious, based upon appropriate medical judgment.

Although all AEs after signing the ICF are recorded in the eCRF, SAE reporting begins after the patient has signed the ICF and has received study treatment. If an SAE occurs after signing the ICF, but prior to receiving study treatment, it needs to be reported ONLY if it is considered reasonably possibly related to study procedure.

Study site personnel must notify Lilly or its designee of any SAE within 24 hours of investigator awareness of the event via a Lilly-approved method. If alerts are issued via telephone, they are to be immediately followed with official notification on study-specific SAE forms. This 24-hour notification requirement refers to the initial SAE information and all follow-up SAE information.

For the time period beginning at treatment allocation through 90 days following cessation of treatment, or 30 days following cessation of treatment if subject initiates new anticancer therapy, whichever is earlier, any SAE, or follow up to a SAE, including death due to any cause other than progression of cancer, whether or not related to the study treatment, must be reported within 24 hours via a Lilly-approved method.

Pregnancy (during maternal or paternal exposure to study treatment) does not meet the definition of an AE but should be reported. To fulfill regulatory requirements, any pregnancy should be reported from the time of treatment allocation through 120 days following cessation of treatment, or 30 days following cessation of treatment if patient initiates new anticancer therapy, whichever is earlier, must be reported by the investigator to collect data on the outcome for both mother and fetus.

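### From about Day 31 to Day 90 after treatment, Table JPCE.2.3 collects only related SAEs while Section 9.2.1 requires all SAEs regardless of relationship, in patients without new anticancer therapy

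*Protocol*

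**What the plan says.** In Table JPCE.2.3 (Post-Treatment Follow-Up Schedule of Activities), the AE collection row is marked for both follow-up phases and carries this instruction: "During long-term follow-up, only SAEs that are related to study regimen or protocol procedure will be collected". Footnote a says that short-term follow-up "ends when final safety assessments are completed 30 days" (±7) after last dose. Footnote b adds: "Long-term follow up begins the day after short-term follow up is completed".

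Section 9.2.1 sets its reporting period in these words: "For the time period beginning at treatment allocation through 90 days following cessation of treatment". It allows a shorter limit, "or 30 days following cessation of treatment if subject initiates new anticancer therapy, whichever is earlier". Within that period it covers any SAE, "whether or not related to the study treatment, must be reported within 24 hours via a Lilly-approved method". The same section later leaves out SAEs caused by disease progression, unless the investigator thinks them possibly related to study treatment.

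Three other places bear on the point:

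- Table JPCE.4.1 names SAEs and ECIs among the primary safety endpoints.
- Section 9.2.1.1 requires ECIs, serious or not, to be reported through 90 days after discontinuation, or 30 days after the start of a new anticancer therapy if that is earlier.
- Section 10.3.3 plans an SAE summary by preferred term within system organ class and gives no last day for it. The same section limits hospitalizations and transfusions to the treatment period plus the 30-day follow-up.

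**The concern.** A site that works from the visit schedule would stop entering unrelated SAEs once the patient passes the safety visit. A site that works from Section 9.2.1 would continue to Day 90. An unrelated SAE on Day 60, in a patient without new therapy, must be reported under one instruction and is not collected under the other.

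The purpose of the trial is to characterize safety, and SAEs are a named part of its primary endpoint. Section 7.4.1.1.2 (Pembrolizumab) says that adverse events linked to that drug may appear several months after the last dose, so the post-treatment period is of real interest. If sites follow different rules, late SAE counts would partly reflect local practice, and entry of a late SAE at some sites would turn on the investigator's causality call. Events not collected at the time cannot be restored by the analysis.

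**Working it through.** There is no plan figure to reproduce. The check sets the instructions side by side and counts days.

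| | Table JPCE.2.3, long-term follow-up | Section 9.2.1 |
|---|---|---|
| Starts | Day after the 30 (±7)-day visit | Treatment allocation |
| Ends | Death or study completion | Day 90 after cessation; Day 30 if new anticancer therapy is started |
| SAEs covered | Related to regimen or procedure only | Any, except caused by progression and not possibly related |

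**Length of the conflict**, taking last dose and cessation of treatment as the same day. Days in conflict = 90 − (day of short-term visit).

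- Visit on Day 23: Day 24 to 90, 90 − 23 = 67 days.
- Visit on Day 30: Day 31 to 90, 90 − 30 = 60 days.
- Visit on Day 37: Day 38 to 90, 90 − 37 = 53 days.

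**Who is affected.** If new anticancer therapy is started, the Section 9.2.1 limit is Day 30. What remains is at most 30 − 23 = 7 days, and only when the visit is held early. The conflict therefore concerns patients without new therapy.

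**Which events are affected.** SAEs judged related fall under both rules. SAEs caused by progression and not possibly related fall under neither. The events in dispute are SAEs judged unrelated and not caused by progression. ECIs are in a similar position: Section 9.2.1.1 wants them, including non-serious ones, during these weeks, and the table row has no place for them unless they are related SAEs.

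**Can the texts be reconciled?**

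- One says collected and the other says reported. Section 9.2 requires the investigator to record all relevant AE and SAE information in the CRF, so an SAE that must be reported cannot also be one that is not collected.
- Section 9.2.1 relieves investigators of actively seeking events once a patient has discontinued or completed the study. A patient in long-term follow-up has not yet done so.
- No passage gives one of the two precedence.

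**Number of patients.** The documents give neither a rate of late unrelated SAEs nor the share of patients without new therapy. Let *r* be the chance of such an SAE per 30 days and *f* the share of 75 patients without new therapy; both are assumptions. Expected patients over 60 days = 75 × *f* × [1 − (1 − *r*)²].

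- *r* = 2%, *f* = 30%: 75 × 0.3 × 0.0396 = 0.9.
- *r* = 10%, *f* = 100%: 75 × 1.0 × 0.19 = 14.25.

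The answer moves about 16-fold (14.25 / 0.9) on assumptions that the documents cannot narrow. It is not an estimate of the effect.

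**The case against.** The best case on the other side is that Section 9.2.1 already gives sites an explicit, mandatory 24-hour rule, so the table row is only a loose summary. That does not settle it: the row says that only related SAEs are collected, and nothing subordinates it to Section 9.2.1.

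Other parts of the objection stand and limit the point.

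- *A size in percentage points.* A reader might apply assumed SAE rates to all 25 patients of a cohort, or all 75, and quote a shift in SAE incidence. The documents do not support that. Patients who start new therapy leave the disputed period, progression events are carved out, patients still on treatment have not reached it, and a patient with an earlier SAE is already counted in overall incidence.
- *A third rule in Section 7.8.1.* A reader might take "Long-term follow-up does not apply" as cutting SAE reporting off at the 30-day visit. That sentence concerns the follow-up phase once continued access begins, which under Section 7.8 comes after the final OS analysis. It states no SAE scope and does not change Section 9.2.1.
- *A flawed primary analysis.* A reader might conclude that the SAE summary itself is wrong. Section 10.3.3 leaves its window open, and the statistical analysis plan, which is not at hand, may set one. A cut at 30 days would largely remove the effect on that summary. It would not resolve the conflicting site instructions.
- *Lost immune-related events.* Late SAEs that the investigator judges related are captured under either rule. Confusion of immune events with progression would arise under both and is not caused by the table.

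The safety analysis is also descriptive, and Section 10.1 says that its precision figures serve no decision criterion.

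**Conclusion.** The contradiction is in the current text and cannot be read away. It lasts 60 days nominally (53 to 67 with the visit window). It applies to patients without new anticancer therapy and to SAEs judged unrelated and not caused by progression, with a parallel gap for ECIs. Within those limits, capture of part of a named primary-endpoint component depends on which passage a site follows. The day count assumes that last dose and cessation of treatment coincide and takes the new-therapy clause literally. The number of patients affected cannot be derived from the documents.

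This is an internal inconsistency that should be fixed. It is not a defect of the design, and no test or decision rule depends on it.

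**What to change.** Reword the AE collection row of Table JPCE.2.3 along these lines: *All SAEs, regardless of relationship, are collected through the end of the reporting period in Section 9.2.1, and ECIs through the period in Section 9.2.1.1; thereafter only SAEs related to study regimen or protocol procedure are collected.* Align the eCRF completion instructions with it. The row should cite the two sections rather than one day count, because their new-therapy clauses run from different dates: cessation of treatment for SAEs, and start of the new therapy for ECIs. Section 7.8.1 and Table JPCE.2.4 need no change for this purpose.

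The cost is protocol wording and eCRF instructions, with no added visit. The small burden is that sites must ask about and enter unrelated SAEs up to Day 90. If the 90-day contacts are counted from the 30-day visit, the first falls near Day 120 (30 + 90), so some of that enquiry will look back over a period already closed.

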## Post-Treatment Follow-Up Schedule of Activities

| Visit                                                             | Short-Term
Follow-Up a                      | Long-Term
Follow-Up b | Instructions                                                                                                                                                                                                                                               |
|-------------------------------------------------------------------|-----------------------------------------------------------|-------------------------------------|------------------------------------------------------------------------------------------------------------------------------------------------------------------------------------------------------------------------------------------------------------|
|                                                                   | 801                                                       | 802-8XX                             |                                                                                                                                                                                                                                                            |
| Procedure                                                  |                                                           |                                     |                                                                                                                                                                                                                                                            |
| Collection of survival information                                |                                                           | X                                   | Although preferable to collect during a clinic visit, survival information may be collected by contacting the patient or family directly (for example, via telephone) if no procedures are required. This should be collected approximately every 90 days. |
| Collection of post-study-treatment anticancer therapy information | X                                                         | X                                   | Perform every 90 days for the first 2 years after discontinuation from study treatment and every 6 months ( $\pm 14$ days)] thereafter until death or study completion.                                                                                    |
| Hematology                                                        | X                                                         |                                     | See Appendix 3                                                                                                                                                                                                                             |
| Coagulation                                                       | X                                                         |                                     | PT or INR and aPTT should be collected at the mandatory Safety Follow-Up Visit after discontinuation of study therapy.                                                                                                                                     |
| Clinical chemistry                                                | X                                                         |                                     | See Appendix 3                                                                                                                                                                                                                             |
| Thyroid Function                                                  | X                                                         |                                     | See Appendix 3                                                                                                                                                                                                                             |
| MDASI* questionnaire                                              | X                                                         |                                     | Patients should complete before interaction with site staff                                                                                                                                                                                                |
| Sample collection                                                 | For all sample collection, see Appendix 4 |                                     |                                                                                                                                                                                                                                                            |
| Biomarkers                                                        |                                                           |                                     |                                                                                                                                                                                                                                                            |

Abbreviations: AE = adverse event; aPTT = activated partial thromboplastin time; CT = computer tomography; CTCAE = Common Terminology Criteria for Adverse Events (NCI 2009); ECOG = Eastern Cooperative Oncology Group; INR = international normalized ratio; irRECIST = immune-related Response Evaluation Criteria in Solid Tumors; MDASI = MD Anderson Symptom Inventory questionnaire, \*= inclusion of a supplemental sheet consisting of 2 additional items (worst cough and worst diarrhea); MRI = magnetic resonance imaging; PT = prothrombin time; RECIST 1.1 = Response Criteria in Solid Tumors Version 1.1; SAE = serious adverse event.

a Short-term follow up starts the day after the patient and the investigator agree that the patient will no longer continue study treatment and ends when final safety assessments are completed 30 days ( $\pm 7$ ) after last dose of study drug.

b Long-term follow up begins the day after short-term follow up is completed and continues every 90 days until the patient's death or overall study completion.

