### 9.2. Adverse Events

The investigator will use Common Terminology Criteria for Adverse Events (CTCAE) Version 4.0 (NCI 2009) to assign AE terms and severity grades.

Investigators are responsible for:

- monitoring the safety of patients in this study and for alerting Lilly or its designee to any event that seems unusual, even if this event may be considered an unanticipated benefit to the patient
- the appropriate medical care of patients during the study
- documenting their review of each laboratory safety report
- following, through an appropriate health care option, AEs that are serious or otherwise medically important, considered related to study treatment or the study, or that caused the patient to discontinue study treatment before completing the study. The patient should be followed until the event resolves, stabilizes with appropriate diagnostic evaluation, or is reasonably explained. Frequency of follow-up evaluation is left to the discretion of the investigator.

Progression of the cancer under study is not considered an AE unless it is considered to be drug-related by the investigator.

After the ICF is signed, study site personnel will record via eCRF the occurrence and nature of each patient's preexisting conditions, including clinically significant signs and symptoms of the disease under treatment in the study. In addition, study site personnel will record via eCRF any change in the preexisting conditions and any new conditions as AEs. Investigators should record their assessment of the potential relatedness of each AE to study procedure or study treatment via eCRF. From the time of treatment allocation through 30 days following cessation of treatment, all AEs must be reported by the investigator.

The investigator will record all relevant AE/SAE information in the CRF.

The investigator will interpret and document whether or not an AE has a reasonable possibility of being related to study treatment or a study procedure, taking into account the disease, concomitant treatments, or pathologies. A "reasonable possibility" means that there is a cause and effect relationship between the study treatment and/or study procedure and the AE.

Planned surgeries and nonsurgical interventions should not be reported as AEs unless the underlying medical condition has worsened during the course of the study.

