### **10.3.3. Primary Outcome and Methodology (Safety and Tolerability)**

The primary objective is to evaluate safety and tolerability of abemaciclib in combination with pembrolizumab. All patients who receive at least 1 dose of study treatment will be evaluated for safety and toxicity. Adverse event terms and severity grades will be assigned by the investigator using CTCAE, Version 4.0.

Safety analyses will include summaries of the following:

- The CTCAE Version 4.0 term reported by the investigator will be mapped to the Medical Dictionary for Regulatory Activities (MedDRA) Preferred Term (PT) and System Organ

Class (SOC) using the corresponding MedDRA Lower Level Term (LLT), unless the reported CTCAE term is ‘Other – specify.’

- If the reported CTCAE term is ‘Other – specify,’ the MedDRA LLT, PT, and SOC centrally mapped from the verbatim AE term will be used.
- All listings and summaries will use the PT resulting from this process.

Preexisting conditions are defined as AEs that begin prior to the first dose of study drug.

A treatment-emergent adverse event (TEAE) is defined as an event that first occurred or worsened in severity after baseline. Comparisons of preexisting conditions to on-treatment events at the LLT level will be used in the treatment-emergent computation. The following summaries will be produced by PT within SOC: preexisting conditions, SAEs, TEAEs, drug-related TEAEs, and procedure-related TEAEs.

The following summaries will be produced by PT within SOC and maximum CTCAE grade: laboratory-based TEAEs, nonlaboratory-based TEAEs, drug-related laboratory-based TEAEs, and drug-related nonlaboratory-based TEAEs.

Reasons for death will be summarized separately for on-therapy and within 30 days of treatment discontinuation.

Hospitalizations and transfusions during the study treatment period or during the 30-day short-term follow-up period will be summarized by cohort.

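### Table JPCE.2.3 and Section 9.2 disagree on when collection of new non-serious AEs ends: an early Visit 801 can close it up to 7 days before the 30-day reporting period is over

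*Protocol*

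**What the plan says.** **Schedule.** Table JPCE.2.3, footnote a, says that short-term follow-up "ends when final safety assessments are completed 30 days ( $\pm 7$ ) after last dose of study drug". Footnote b adds: "Long-term follow up begins the day after short-term follow up is completed". The AE collection row of the same table limits what is gathered from then on: "During long-term follow-up, only SAEs that are related to study regimen or protocol procedure will be collected". Events already on record are treated differently: "All drug- or procedure-related AEs and SAEs should be followed until they resolve", or until one of several other end points listed in that row is met.

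**Reporting duty.** Section 9.2 sets a period that does not refer to any visit: "From the time of treatment allocation through 30 days following cessation of treatment, all AEs must be reported by the investigator". Section 9.2.1 has a separate rule for serious AEs (SAEs), related or not. It opens "For the time period beginning at treatment allocation through 90 days following cessation of treatment" and shortens to 30 days if new anticancer therapy starts.

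**Analysis.** TEAEs are among the primary endpoints (Table JPCE.4.1). Section 10.3.3 defines them without a post-treatment end date: "A treatment-emergent adverse event (TEAE) is defined as an event that first occurred or worsened in severity after baseline". The same section uses a 30-day period for deaths and for two other summaries: "Hospitalizations and transfusions during the study treatment period or during the 30-day short-term follow-up period will be summarized by cohort".

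**The concern.** The schedule closes full AE collection by an act, completion of Visit 801, which may be done before Day 30. Section 9.2 closes it by a date, Day 30. For a patient seen on Days 23 to 29 the two instructions cannot both be met as written. The schedule says that only related SAEs are collected from the next day, while Section 9.2 says that everything is reported for up to another week.

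Sites usually work from the schedule, and after an early visit it provides no further full AE contact before Day 30. For patients in short-term follow-up when continued access begins, Section 7.8.1 says that long-term follow-up does not apply, so Visit 801 is their last scheduled contact.

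Safety is the only primary objective, and each cohort has about 25 patients. The Protocol itself warns, in its pembrolizumab dose-adjustment section, that AEs can appear months after the last dose, so the days after treatment cannot be assumed empty of events. Because the TEAE definition has no end date, the period over which TEAEs are observed after treatment depends on how long events are collected.

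**Working it through.** **Inputs**

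| Input | Value | Source |
|---|---|---|
| Visit 801 | 30 ± 7 days after last dose | Table JPCE.2.3, footnote a |
| Start of long-term follow-up | day after short-term follow-up is completed | Table JPCE.2.3, footnote b |
| New AEs collected in long-term follow-up | related SAEs only | Table JPCE.2.3, AE collection row |
| End of the all-AE reporting period | 30 days after cessation of treatment | Section 9.2 |

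Two assumptions are needed because the Protocol does not settle them:
- Footnote a counts from the last dose of study drug and Section 9.2 from cessation of treatment. I take these as the same date.
- No distribution of visit dates is given. For the averages I take visits as equally likely on each of Days 23 to 37.

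**Step 1: the window.** Earliest visit 30 − 7 = Day 23; latest 30 + 7 = Day 37.

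**Step 2: uncovered days for one patient.** For a visit on day v, long-term follow-up starts on day v + 1. The days of the Section 9.2 period left without full AE collection are max(0, 30 − v).

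| Visit day | Long-term follow-up starts | Uncovered days | Share of 30 days |
|---|---|---|---|
| 23 | Day 24 | 7 | 7/30 = 23.3% |
| 30 | Day 31 | 0 | 0% |
| 37 | Day 38 | 0 | 0% |

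**Step 3: averages under even spread.**
- Possible visit days: 15. Days that leave a gap: 23 to 29, that is 7.
- Share of patients affected: 7/15 = 47%.
- Total uncovered days over the seven early visit days: 7 + 6 + 5 + 4 + 3 + 2 + 1 = 28.
- Mean among affected patients: 28/7 = 4 days.
- Mean over all patients: 28/15 = 1.9 days, or 1.87/30 = 6.2% of the period.

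**Step 4: after the fix.** If collection runs to the later of Visit 801 and Day 30, or the visit cannot fall before Day 30, then max(0, 30 − v) no longer applies or is 0 for every patient.

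The documents give no AE rate for this period, so the days cannot be turned into a number of missed events.

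**The case against.** The strongest reply is that nothing is cut off. Section 9.2 obliges investigators to report all AEs through 30 days and makes no exception for an early visit; the ±7 only says when the visit may take place. A site that follows Section 9.2 loses nothing. This stands in part: it means that a shortfall is possible rather than certain. It does not remove the conflict, because the AE row says in terms that only related SAEs are collected once long-term follow-up has begun.

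Other replies also stand and limit the point:

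- **TEAE window.** A reader might infer that the primary endpoint has a 30-day post-treatment window of which part is lost. Section 10.3.3 sets no such limit for TEAEs. The 30 days is the reporting period of Section 9.2 and the summary window for deaths, hospitalizations and transfusions.
- **Deaths and hospitalizations.** A reader might count these among the losses. An AE that leads to hospitalization is an SAE and falls under the longer rule of Section 9.2.1, as does death from causes other than progression. Transfusions are not listed among the primary endpoints.
- **Later contact.** It would be too strong to say that every patient is next seen about 90 days later. Patients who stop without objective progression keep their scan schedule, and related AEs already recorded are still followed.
- **Use of the results.** There is no control group, and Section 10.1 describes its interval figures as a reference, not as decision criteria. No comparison between randomized groups or formal rule is at stake.

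The same AE row also sits badly with the 90-day SAE rule: from Visit 801 to Day 90 is 90 − 37 = 53 to 90 − 23 = 67 days in which the table omits unrelated SAEs. That is a larger and separate conflict, and it does not cancel this one.

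**Conclusion.** The point holds as an internal contradiction over when collection of new non-serious AEs ends. For a patient seen before Day 30, following Table JPCE.2.3 stops collection up to 7 days (23%) before the Section 9.2 period is over. Given an even spread of visits and a common start date for the two clocks, about 47% of patients would be affected, by 4 days each on average, or 1.9 days over all patients. If sites hold Visit 801 mostly on or after Day 30, or apply Section 9.2 regardless of the visit, the effect is close to nil.

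A reader might conclude that TEAE incidence will be understated. The documents support only a risk of modest under-collection: they contain both the shorter and the longer instruction, and do not say which prevails. Reconciling them is worthwhile because these AEs feed the sole primary objective and the change is cheap.

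**What to change.** Reconcile the two passages in one of two ways:

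1. Add to the AE collection row of Table JPCE.2.3 that all AEs are collected to the later of Visit 801 and Day 30, with a telephone AE check at Day 30 when the visit was held earlier. This keeps the ±7 window.
2. Change footnote a so that Visit 801 falls at 30 (+7) days, that is Days 30 to 37.

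In the same edit, use one start date for both clocks. Whether post-treatment summaries are cut at Day 30 for patients seen later can be left to the SAP.

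The cost is a line of text, plus one telephone call per early visit under the first option or a little less scheduling freedom for sites under the second.
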